### Acceptability

#### Overview

Acceptability will be assessed using multiple indicators capturing participants’ and caregivers’ perspectives on the intervention and study procedures. Measures will include treatment satisfaction, therapeutic alliance (youth, caregiver, and therapist versions), ratings of digital treatment usability and engagement, and evaluation of individual exercises. In addition, qualitative interviews with adolescents, caregivers, and therapists will explore perceived helpfulness, burden, and acceptability of the blended format.

#### Therapeutic Alliance

Therapeutic alliance will be measured using a brief 6-item questionnaire based on Bordin’s working alliance theory and adapted from versions of the Working Alliance Inventory [44]. Items will assess agreement on goals, collaboration on tasks, and the emotional bond using a 7-point scale (0‐6), where higher scores indicate a stronger alliance. Youth, caregivers, and therapists will complete parallel forms. Although the adapted version has not undergone formal validation, its use is considered appropriate for a pilot feasibility study, as it provides a brief, pragmatic assessment of alliance across respondent groups, consistent with recommendations for pilot and feasibility trials [34].

#### Digital Treatment Evaluation

Digital treatment evaluation will assess usability, engagement, and perceived helpfulness of the web-based components. Youth and caregivers will complete an 11-item scale rated on a 5-point Likert scale (0‐4), informed by established usability and technology acceptance frameworks. Higher scores will indicate greater usability, satisfaction, and perceived therapeutic value.

#### Exercise Evaluation

The exercise evaluation will capture youths’ and caregivers’ experiences with the exercises introduced during the web-based stabilization phase. Each exercise will be rated from −2 (very negative) to +2 (very positive), with “X” indicating noncompletion. The measure will provide insight into acceptability and identify exercises requiring refinement. Higher scores indicate a more positive experience, while consistently negative ratings may signal the need for modification.

#### Treatment Satisfaction (Youth)

Treatment satisfaction will be assessed using a structured measure that evaluates perceived helpfulness, quality of the therapeutic relationship, satisfaction with delivery formats (web-based application, video, and in-person), and perceived improvement. Items will be rated on Likert-type scales, with optional free-text responses. Higher scores will represent greater satisfaction.

### Exploratory and Clinical Outcomes

#### Overview

Exploratory clinical outcomes will be collected to examine preliminary patterns of symptom change, estimate variability, and inform outcome selection and sample-size calculations for a future fully powered noninferiority trial. Consistent with recommendations for pilot and feasibility studies, these analyses will be descriptive in nature and will not include formal hypothesis testing.

#### Child and Adolescent Trauma Screen, Version 2

The Child and Adolescent Trauma Screen, version 2 (CATS-2), will measure trauma exposure and PTSD symptoms. The instrument includes a checklist of 16 potentially traumatic events and 25 symptom items assessing re-experiencing, avoidance, negative mood/cognition, and hyperarousal. Symptoms are rated on a 4-point scale (0‐3), with total scores ranging from 0 to 60. CATS-2 has demonstrated strong reliability and validity in child and adolescent populations [45].

#### Children’s Revised Impact of Event Scale, 13-Item Version

The Children’s Revised Impact of Event Scale, 13-item version (CRIES-13), will assess posttraumatic stress reactions, including intrusion, avoidance, and arousal. The scale contains 13 items rated on a 4-point scale (0, 1, 3, and 5), yielding a total score of 0‐65, with higher scores indicating greater symptom severity. CRIES-13 has demonstrated good reliability and validity across youth samples, including in Swedish clinical contexts [46].

#### Dissociation Screening Questionnaire, 12-Item Version

The Dissociation Screening Questionnaire, 12-item version (DSQ-12), will screen for psychoform and somatoform dissociative symptoms. It consists of 12 items rated on a 5-point Likert scale (0‐4), with higher scores indicating more severe dissociation. DSQ-12 was developed and validated in Swedish adolescent samples and demonstrates strong reliability, convergent validity, and a stable factor structure [47].

#### Compassionate Engagement and Action Scales for Youth – Swedish Version

The Compassionate Engagement and Action Scales for Youth – Swedish Version (CEASY-SE) will measure compassion-related processes across 3 flows: compassion for self, compassion for others, and compassion received from others. Items are scored on a 10-point scale (1‐10), with higher scores reflecting stronger compassion skills. The Swedish adolescent version has shown good internal consistency and construct validity in both community and clinical samples [25,26].

#### Difficulties in Emotion Regulation Scale, 16-Item Version

The Difficulties in Emotion Regulation Scale, 16-item version (DERS-16), will assess broad difficulties in emotion regulation across 6 domains, including nonacceptance of emotions, limited access to strategies, and difficulty engaging in goal-directed behavior when distressed. The 16 items are rated on a 5-point scale (1-5), with higher scores reflecting greater dysregulation. DERS-16 has demonstrated strong reliability and validity across adolescent and clinical populations [48].

#### Montgomery-Åsberg Depression Rating Scale for Youth

The Montgomery-Åsberg Depression Rating Scale for Youth (MADRS-Y) will assess depressive symptoms and suicidality through 9 items scored on a 7-point scale (0‐6), yielding total scores from 0 to 54. Items assess sadness, concentration, lassitude, and sleep disturbances, with one item specifically targeting suicidal thoughts. The Swedish validation demonstrates good reliability and clinical utility in adolescent psychiatric samples [49].

#### Revised Child Anxiety and Depression Scale, 47-Item Version

The Revised Child Anxiety and Depression Scale, 47-item version (RCADS-47), will measure symptoms across 6 domains: separation anxiety, social phobia, generalized anxiety, panic disorder, obsessive-compulsive symptoms, and major depression. Items are rated on a 4-point scale (0‐3), with higher scores indicating greater severity. RCADS has strong psychometric support internationally and has been widely used in Nordic youth contexts [50].

#### Trauma-Related Shame Inventory

The Trauma-Related Shame Inventory (TRSI) will assess shame-based cognitive and emotional responses to trauma, including self-blame, negative self-evaluation, feelings of exposure, and avoidance urges. Items are rated on a 5-point scale (0‐4). TRSI has demonstrated adequate reliability and validity among trauma-exposed youth and adults, although no Swedish validation is currently available [16].

#### Trauma-Related Guilt Inventory

The Trauma-Related Guilt Inventory (TRGI) will measure guilt cognitions, emotional distress, and avoidance behaviors following traumatic events. The 32 items are rated on a 5-point Likert scale (0‐4), producing both subscale and total scores. TRGI has shown strong psychometric properties across diverse trauma-exposed populations, though no Swedish validation exists [51].

#### Parental Stress Scale

The Parental Stress Scale will assess caregivers’ emotional stress related to the parenting role, including perceived rewards, demands, and strain. The scale contains 18 items rated on a 5-point scale (1-5), with higher scores indicating greater parental stress. A recent Swedish validation demonstrates good internal consistency and a robust 2-factor structure in both community and clinical samples [52].

### Analysis

#### Quantitative Analysis

All quantitative analyses will follow the intention-to-treat principle [53], including all randomized participants in their assigned condition. Consistent with recommendations for pilot and feasibility trials, analyses will focus on estimating feasibility and acceptability metrics using descriptive statistics (eg, proportions, means, and 95% CIs). These outcomes will be interpreted in relation to predefined progression criteria to inform decisions about trial procedures.

Clinical and process outcomes will be analyzed descriptively, with a focus on estimation and patterns rather than formal hypothesis testing. To support interpretability, these outcomes will be organized into predefined conceptual domains (eg, clinical symptoms, compassion-related processes, and emotion regulation) and interpreted in terms of overall patterns across related measures rather than individual statistical significance.

Exploratory clinical outcomes will be examined to describe symptom trajectories and estimate variability, thereby informing the design of a future, fully powered noninferiority trial. Baseline-adjusted analysis of covariance models and linear mixed effects models will be used descriptively to examine patterns of change over time across study conditions and to generate variance estimates and confidence intervals, rather than to formally test between-group differences. Individual-level changes will be assessed using the Reliable Change Index [54,55]. All analyses will be conducted using standard statistical software (eg, R or SPSS).

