### Sample Size

As this is a pilot RCT, the sample size is set at 40 adolescents (20 per arm). This sample size is expected to enable estimation of key feasibility parameters, including recruitment, retention, adherence, and data completeness, as well as estimates of variability in outcome measures [34,35]. The selected sample size also reflects practical considerations related to recruitment within rural child and adolescent psychiatric services [36,37]. No formal power calculation will be conducted, as the trial is not designed to test intervention effectiveness but to inform the design and sample size planning for a future fully powered noninferiority trial.

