### Recruitment and Randomization

Participants will be recruited through child and adolescent psychiatry clinics in the regions of Norrbotten and Västerbotten. Clinicians or research staff will provide information about the study to potentially eligible adolescents and caregivers during routine clinical contacts, after which interested families will be invited to undergo eligibility screening and informed consent.

Following completion of baseline assessments, eligible participants will be randomized in a 1:1 ratio to either bTF-CBT-C or standard TF-CBT. An independent researcher not involved in recruitment or treatment will generate a computer-based randomization sequence using permuted blocks (block size=4) to maintain balance between study arms. Randomization will be stratified by geographic region to account for contextual differences between sites.

Allocation will be concealed using sequentially numbered, sealed, opaque envelopes prepared by the independent researcher. Envelopes will be opened only after baseline assessments are finalized. Due to the nature of psychological treatment, therapists and participants cannot be blinded to group assignment; however, outcome assessors will remain blinded whenever feasible to minimize assessment bias.

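### Randomisation is stratified by region, but the article names no region term in the models whose variances feed noninferiority planning; if region is prognostic, those variances and intervals will be modestly overstated

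*Protocol article*

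**What the plan says.** Under Recruitment and Randomization: "Participants will be recruited through child and adolescent psychiatry clinics in the regions of Norrbotten and Västerbotten". Allocation is 1:1, using "permuted blocks (block size=4) to maintain balance between study arms", and "Randomization will be stratified by geographic region to account for contextual differences between sites". Region is the only stratification factor, and the stated reason for it is that sites are expected to differ. The limitations part of the Discussion likewise expects treatment delivery to vary between regions.

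Under Quantitative Analysis: "Baseline-adjusted analysis of covariance models and linear mixed effects models will be used descriptively", with the purpose "to generate variance estimates and confidence intervals, rather than to formally test between-group differences". The Results and Discussion sections then say that the variance estimates will inform the sample size and margin of the future noninferiority trial.

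No section names region, site or the stratification factor as a model term, and no section excludes it. Under Sample Size, the trial has 40 adolescents, 20 per arm, and "No formal power calculation will be conducted".

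**The concern.** Stratified blocks balance region across the arms, so a regional difference in outcome largely drops out of the arm contrast. A model without region does not credit this. It leaves the between-region component in the residual, so the residual variance and the standard error of the arm contrast come out larger than the design warrants.

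In many trials this would be a small loss of precision in a test. Here there is no test: the variance and the interval are the product of these models. A residual variance that contains a regional component would, if carried forward, make the next trial somewhat larger than it needs to be. The Sample Size section cites practical limits on recruitment in rural services, so extra participants have a real cost.

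**Working it through.** The article states no SD, residual variance, interval width or power, so there is no figure of its own to reproduce. The check compares ANCOVA with arm and baseline against ANCOVA with arm, baseline and region.

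**Inputs from the article:** N = 40; 1:1 allocation; blocks of 4; two strata, taking each named region as one stratum; 70% retention as the progression threshold, so 0.70 × 40 = 28 analysed.

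**Assumed inputs:** the difference between regions, d, in units of the residual SD, from 0 to 0.8; equal region sizes; baseline–outcome correlation 0.5 in the simulation.

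**Formulas.**
- Partial R² of region with two equal regions: R² = (d²/4) / (1 + d²/4).
- Residual variance ratio, region omitted over included: 1/(1 − R²).
- Interval width ratio: √[1/(1 − R²)] × t(0.975, N − 3)/t(0.975, N − 4). At N = 40 the ratio of t values (37 and 36 df) is 0.9991; at N = 28 it is 0.9979.

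**Worked case, d = 0.5.** R² = 0.0625/1.0625 = 0.059. Variance ratio = 1.0625. Width ratio = √1.0625 × 0.9991 = 1.030.

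**Analytic results over a range of R², N = 40:**

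| Partial R² | Variance ratio | Width ratio |
|---|---|---|
| 0 | 1.00 | 0.999 |
| 0.01 | 1.01 | 1.004 |
| 0.05 | 1.05 | 1.025 |
| 0.10 | 1.11 | 1.053 |
| 0.20 | 1.25 | 1.117 |

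With exact arm balance within regions, the two models give equal widths at R² of about 0.002 (N = 40) or 0.004 (N = 28).

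**Simulation** (8,000 runs per scenario, stratified blocks of 4, on average equal regions; Monte Carlo standard error of coverage about √(0.95 × 0.05/8000) = 0.24 points):

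| d | Variance ratio, N = 40 | Width ratio, N = 40 | Coverage without / with region, N = 40 | Width ratio, 30% loss |
|---|---|---|---|---|
| 0 | 1.000 | 0.998 | 95.3% / 95.3% | 0.991 |
| 0.2 | 1.010 | 1.003 | 95.1% / 94.9% | 0.995 |
| 0.5 | 1.065 | 1.030 | 95.9% / 95.2% | 1.023 |
| 0.8 | 1.166 | 1.078 | 96.4% / 95.0% | 1.068 |

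**Downstream size.** Assume a margin of 0.4 region-adjusted SD, one-sided 0.025 and 80% power. Then n per arm = 2 × (1.960 + 0.842)² / 0.4² = 98.1, so 99. Multiplying 98.1 by the analytic variance ratio for d = 0.2, 0.5 and 0.8 (1.010, 1.0625 and 1.16) gives 100, 105 and 114 per arm.

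**Against sampling error.** A variance estimated on 37 df has a 95% chi-square interval of about −34% to +67% around the estimate; on 25 df (28 analysed) it is about −38% to +91%.

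**The case against.** The strongest objection is that the article never says the models adjust for baseline alone. Its description names a type of model, not a closed covariate list. It gives no random effects or covariance structure, and the baseline adjustment may grammatically apply only to the ANCOVA. An article commonly leaves such detail to a fuller document. This stands as far as it goes: a reader might infer that region has been ruled out, and the text does not support that. What remains is that the article does choose to state an adjustment, and the one it states leaves out its own stratification factor.

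A reader might also infer that the variances and intervals are bound to be too large. That is not supported either. It requires region to predict outcome after baseline adjustment, and the article gives no figure for this. An R² of 0.10 would need a gap of about 0.67 residual SD between equal regions, and nothing in the article shows a gap of that size. With no gap, omitting region gives marginally narrower intervals; with 30% loss this also holds at 0.2 SD.

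Three further points stand. The shift is small beside the sampling error of a variance from 40 or fewer participants. Any error is towards wider intervals, with no test at stake. The progression criteria use recruitment, retention, acceptability ratings and data completeness, none of which comes from these models. It is also fair that the variance estimates are only said to inform the next trial's size, which may involve other sites. These points limit the weight of the concern. They do not make leaving region out the better choice.

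**Conclusion.** A minor point that holds conditionally. The article stratifies by region because it expects sites to differ, yet names only baseline as an adjustment in the models that supply planning variances. If region is prognostic and omitted, the residual variance is overstated by about 6% and interval width by about 3% for an assumed 0.5 SD difference between two equal regions at N = 40. At an assumed 0.8 SD the figures are about 17% and 8%. If regions do not differ, there is essentially no effect.

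The result rests on the assumed regional difference, on two strata of similar size, and on the planned trial adjusting for its own stratification factor, so that the region-adjusted residual is the matching planning variance. It is a loss of efficiency in exploratory output. It does not threaten validity.

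**What to change.** In Quantitative Analysis, state that the ANCOVA and linear mixed effects models include baseline score and region (the stratification factor) as fixed effects. State also that the residual variance used for sample size planning comes from that model.

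The cost is one phrase and one degree of freedom. Region is already known for every participant at randomisation. If region turns out to have no effect, intervals widen by about 0.2% at N = 40 (1/0.998) and by about 1% when some 30% of participants are lost (1/0.991). Trial Status reports 6 participants enrolled at submission in May 2026, so the change can still be fixed well before any outcome analysis.

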#### Missing Data

Patterns of missing data will be examined to evaluate the assumptions of missing at random. For exploration analyses, multiple imputation will be applied as appropriate. Mixed effects models will use full-information maximum likelihood estimation, which accommodates incomplete data.

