**Methods:**

A 2-arm parallel-group pilot RCT will randomize 40 adolescents (12‐17 years) with *DSM-5* (*Diagnostic and Statistical Manual of Mental Disorders* [Fifth Edition]) PTSD to bTF-CBT-C or standard TF-CBT in routine child and adolescent psychiatric services. The intervention includes an approximately 5-week web-based stabilization phase, followed by 7‐14 therapist-led sessions delivered primarily via videoconference, with some in-person sessions. Primary outcomes will assess feasibility (recruitment, retention, adherence, data completeness, and adverse events) and acceptability (satisfaction, alliance, and qualitative interviews). Exploratory outcomes include PTSD symptoms, self-compassion, emotion regulation, depression, anxiety, suicidality, and dissociation. Assessments will be conducted at baseline, poststabilization, posttreatment, and 6-month follow-up. Feasibility and acceptability will be summarized descriptively. Exploratory analyses using analysis of covariance and mixed effects models will estimate variance parameters, confidence intervals, and descriptive change trajectories without hypothesis testing. Qualitative data will be analyzed using reflexive thematic analysis.

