**Figure 1. F1:**
[figure not shown]
CONSORT flowchart of participants.

Feasibility and acceptability outcomes will be presented using descriptive statistics (eg, proportions, means, and 95% CIs) across assessment time points. Estimates of variance in clinical outcomes will be used to inform sample size calculations for a future fully powered noninferiority trial, including the specification of an appropriate noninferiority margin. Exploratory outcomes will be reported as patterns of change over time using descriptive summaries and graphical representations of symptom trajectories. Additional visualizations (eg, line plots of symptom change and summary figures of feasibility indicators) will be used to enhance interpretability.

Qualitative findings will be presented as themes developed through reflexive thematic analysis and integrated with quantitative indicators to provide a comprehensive understanding of feasibility, acceptability, and user experiences. Together, these results will inform the refinement of the intervention and the key design parameters for a future fully powered trial. If predefined feasibility thresholds are not met (eg, retention below prespecified levels), the research team will review potential barriers and consider modifications to study procedures or intervention delivery prior to a future trial.

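### The mixed models are fixed to full maximum likelihood, which makes their variance estimates modestly too small (about 5-10%) for the sizing use the plan gives them

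*Protocol article*

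**What the plan says.** The estimator is named once, in the protocol article under Missing Data: "Mixed effects models will use full-information maximum likelihood estimation, which accommodates incomplete data". Coping with incomplete data is the only reason given. REML is not mentioned.

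The purpose of the models is stated under Quantitative Analysis: "Baseline-adjusted analysis of covariance models and linear mixed effects models will be used descriptively", in part "to generate variance estimates and confidence intervals, rather than to formally test between-group differences". The abstract likewise lists variance parameters and confidence intervals as the output. The Results section says where they go: "Estimates of variance in clinical outcomes will be used to inform sample size calculations for a future fully powered noninferiority trial". It adds the noninferiority margin as a further use, and the Discussion repeats both uses.

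The trial randomises 40 adolescents, 20 per arm (Sample Size). On visits, the abstract says: "Assessments will be conducted at baseline, poststabilization, posttreatment, and 6-month follow-up". On the strata: "Randomization will be stratified by geographic region to account for contextual differences between sites". The progression criterion for retention is 70% at the postintervention assessment, which is 28 of 40.

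**The concern.** Estimating a variance is one of the declared jobs of these models, and it is the job that ML does least well in a small sample. ML treats the fitted means as known, so it divides the residual sum of squares by the number of participants instead of the remaining degrees of freedom. The result is always biased downward. REML makes the correction.

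Incomplete data are no reason to prefer ML. Both methods are likelihood methods, both use every available observation, and both rest on missing at random.

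The required sample size of the later trial is proportional to the variance. A variance biased low therefore pushes that trial towards being too small. Standard errors from the same fit are also slightly too small.

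**Working it through.** The article gives no variance, margin or power figure, so there is nothing of its own to reproduce. The size of the bias follows from the number of participants and the number of fitted parameters.

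**Inputs from the article.** 40 participants, 20 per arm; four visits; two regions as strata; 70% retention threshold, 28 participants. **Assumptions.** For the simulation: random-intercept model, total variance 100, within-person correlation 0.5. For the later trial: SD 10, margins 3 to 5, one-sided 2.5% level, 80% power.

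**Step 1, closed form.** For the variance at one visit with n participants and p between-person fixed effects, expected ML variance / true variance = (n − p)/n. Here p = 2 is the two arm means, p = 3 adds baseline or region, and p = 4 adds both.

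| n | p = 2 | p = 3 | p = 4 |
|---|---|---|---|
| 40 | 38/40 = 0.950 | 37/40 = 0.925 | 36/40 = 0.900 |
| 28 | 26/28 = 0.929 | 25/28 = 0.893 | 24/28 = 0.857 |

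The variance is 5-10% low with everyone observed and 7-14% low with 28. The n = 28 row is the harsher case, since a mixed model also borrows from earlier visits.

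**Step 2, simulation.** 400 trials per scenario, fitted with arm by visit plus region.

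| Retention | ML total variance | REML total variance | ML/REML standard error, arm difference at 6 months |
|---|---|---|---|
| 100% | 93.3 | 99.9 | 0.967 |
| 70% | 92.8 | 100.0 | 0.964 |

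The true value is 100, so ML is 6.7% and 7.2% low. The full-retention figure agrees with theory:
- Residual: six visit-related effects are taken from 40 × 3 = 120 within-person degrees of freedom, giving 50 × 114/120 = 47.5.
- Person-mean variance: (50 + 50/4) × 37/40 = 57.8.
- Between-person component: 57.8 − 47.5/4 = 45.9.
- Total: 45.9 + 47.5 = 93.4.

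A separate simulation (correlation 0.6, five model and dropout variants, 3,000 trials each) gave ML totals of 0.90-0.94 of the truth and REML totals of 0.99-1.01.

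**Step 3, consequence if the ML figure sized the later trial.** Per-arm n = 2 × SD² × (1.96 + 0.8416)²/margin². With SD 10 and margin 4 this is 2 × 100 × 7.849/16 = 98.1, so 99. Multiply by the variance ratio, round up, and compute power at the true SD as Φ(√(n/2) × 4/10 − 1.96).

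| Variance ratio | n per arm | True power |
|---|---|---|
| 0.950 | 94 | 78.3% |
| 0.925 | 91 | 77.0% |
| 0.893 | 88 | 75.6% |
| 0.857 | 85 | 74.1% |

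Margins 3 and 5 give nearly the same powers (73.8-78.2%).

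**Step 4, intervals.** Simulated coverage of the nominal 95% ML interval for the 6-month arm difference was 95.2% and 95.0% (REML 96.0% and 95.8%). With 400 runs, one such figure has a standard error of √(0.95 × 0.05/400) = 1.1 points. The separate simulation gave 93.4-94.6% with normal quantiles. For a single-visit analysis at n = 40, the closed form with normal quantiles gives 92.9-93.6% for ML and 94.2-94.3% for REML, so part of that shortfall comes from the quantile and not from ML.

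**Step 5, scale.** The 95% interval for an unbiased variance runs from 0.67 to 1.66 times the estimate at 38 degrees of freedom, and from 0.62 to 1.91 at 25.

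**The case against.** The strongest reply is that the consequence does not follow from the plan. A reader might infer that the variances that will size the noninferiority trial are too small. The article does not support that. Quantitative Analysis names ANCOVA as well as mixed models, the ANCOVA residual mean square is corrected for degrees of freedom, and no section says that the mixed-model figure alone will be used. A future team could also use an upper confidence limit or outside data. This stands, and it makes the power loss conditional.

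A reader might also infer that the pilot's confidence intervals fall materially short of 95%. That is not established: the simulations disagree at the level of a point or so, the article does not specify normal quantiles, and formal testing is ruled out. The progression criteria use no mixed-model output.

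Third, sampling error is several times the bias. This is true, but sampling error goes in both directions and shows in an interval. The ML bias always points towards a smaller later trial and adds to that error.

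Finally, the sentence sits under Missing Data and may be loose wording for a likelihood analysis of all available data, with details left to an analysis plan. An article may leave the estimator open. This one names it, and read literally it sets the software to ML.

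**Conclusion.** The concern holds as a minor point about one of two named variance sources. The article fixes ML for the mixed models while asking them for variance estimates. At 40 participants those estimates are about 5-10% low, up to about 14% at 70% retention with four between-person parameters, and standard errors are about 3-4% too small. The closed-form ratios need only n and p. The simulated figures rest on the assumed random-intercept structure and correlation. The 74-78% power range applies only if the later trial is sized for 80% power on the raw ML point estimate, which the documents do not say will happen. No feasibility conclusion of the pilot is affected.

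**What to change.** In the Missing Data section, replace full-information maximum likelihood with: *restricted maximum likelihood (REML), which also uses all available observations under missing at random*. Add that any mixed-model variance used for the later sample size comes from the REML fit. Kenward-Roger or Satterthwaite degrees of freedom for the intervals would be preferable; their absence from the article is not itself a fault.

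The cost is one sentence. REML is available in both R and SPSS, the packages the article names as examples, and no data collection changes. Reported variances and intervals become slightly larger. The change removes the bias but not the sampling error of a variance estimated from 40 people.
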